## Abstract

**Introduction:**

There is increasing evidence that green care (from nature-in-everyday life and nature-based health promotion to nature-based therapy) can promote mental health and well-being. However, there is contradictory evidence and few large-scale international studies focused on health inequities. The GreenME project aims to identify ways in which effective green care can be scaled-up to improve adult mental health and well-being equity while contributing to multiple socio-ecological co-benefits across the Global North.

**Methods and analysis:**

GreenME’s approach is threefold: (i) to diagnose the current status of green care in project consortium countries through a grey literature review and stakeholder interviews, (ii) to increase scientific evidence on the relationship between green care and mental health and well-being equity using modified randomised controlled trials and a population-level socioecological cross-sectional survey study and (iii) to empower green care actors by co-creating a set of tools with consortium countries’ participating stakeholders. GreenME will: (a) produce a catalogue of identified successful green care models and best practices; (b) design a robust but adaptable protocol for testing the pathways, effectiveness and cost-effectiveness of nature-based therapies; (c) identify the mental health equity impact of green care and (e) co-create solutions for national and EU-level policies and develop online resources for nature-based therapy providers. GreenME is conceptualised and designed to increase the use of green care and its integration within a multi-scalar green care framework which could ultimately promote just and sustainable healthy communities.

**Ethics and dissemination:**

Ethical approval has been obtained individually from each partner/site (UAB CERec 6594, 6851, UAB-CERec180, UAB-CERec178 and CEEAH 7269; UOC CE23-PR29, CE240PR07, CE24-PR59, CE24-PR55; l'Hospital de Mataró CEIm 11/2; CEIm Fundació Sant Joan de Déu PIC-82-25; Alma Mater Stadiorum Universita di Bologna, Proj nos. 0157655, 0075975; ILS, no number ‘Survey in Workpackage 2’, no number ‘Workshops in Workpackage 5’; Swedish Ethics Review Committee, 2024–2810-01, 2025–0195401; University of Kent, CREAG064-04-024; University of Salford Ethics Administration, Ref 0189, 4552; Institute of Psychiatry and Neurology Bioethics Committee, no number; Committees on Ethics and Scientific Research, Res no 32/RKF/2023U). All study results will be disseminated through peer-reviewed publications, scientific conferences and via reports and workshops for stakeholders at the regional (European Union), national and local levels.

**Trial registration number:**

ISRCTN13105773, ISRCTN71485431, ISRCTN11841855, ISRCTN14970007 and ISRCTN15381820.

STRENGTHS AND LIMITATIONS OF THIS STUDYThis study adds a health equity framing across its multiple design elements.We will evaluate existing nature-based therapy interventions, capturing those interventions which have already survived in the real world while gathering missing evidence on their mechanisms and cost-effectiveness.The study gathers population-level mental health and equity data and exposures to green and blue spaces across study sites in seven countries.The trade-offs of evaluating existing interventions may reduce the robustness of the study design.

## Introduction

 At least 15% (95% CI 16.8% to 16.8%) of the population globally lives with mental ill-health.^1^ This is likely to be an underestimate due to widespread stigma towards mental health problems and subsequent underreporting. It is vital to address mental health through an equity lens, which considers the ability of all people to achieve their best possible state of mental health without unfair, avoidable or remediable differences between groups.^2^ Historical, cultural, political and sociodemographic factors impact how mental health problems are unevenly distributed, perceived and addressed.^3^

Mental health problems are the third leading cause of overall disease burden in Europe (including the UK), affecting approximately 150 million people.^4^ However, individuals who are members of marginalised groups (ie, those who have fewer opportunities compared with other social groups and may experience a higher risk of poverty, social exclusion, discrimination and/or violence than the general population due to social, cultural, economic and political conditions or a combination of these conditions; see table 1) experience a disproportionate burden of these problems,^5^ partly due to unequal social and environmental conditions.^6^ For example, rural populations may have less access to mental health services, while those who live in urban areas may face environmental stressors such as air pollution or lack of green space.^7–9^ Moreover, each country and region has context-specific public health challenges.^10^ Addressing the growing burden of mental health problems across the Global North thus requires multifaceted solutions that take country context and the intersectionality of privilege and marginalisation into account.^3^

**Table 1 T1:** Key GreenME terminology

Definitions were drafted and refined by the GreenME terminology working group with consultation from GreenME consortium members	
Nature	Within the context of the GreenME project, **nature** is defined as the natural world, including both its living and non-living aspects such as plants, animals, rocks and water, as well as the processes and phenomena that produce, reproduce and occur within it, such as plant growth and wind and tides. This understanding of nature does not exclude human influence and presence, thus including ‘man-made’ areas (eg, gardens, parks, hiking trails, etc.) as aspects of nature.
Green care	GreenME defines **green care** as a way of conceptualising different ways of engaging with nature that can improve human health and well-being. It is framed within a three-level model from nature-in-everyday life and nature-based health promotion to nature-based therapy.
Nature-based therapy (NBT)	**Nature-based therapy** is a therapeutic intervention directed by a trained facilitator in an indoor or an outdoor setting that includes exposure to and interaction with nature to enhance individuals’ physical and mental health and well-being. Examples of NBTs: participating in a structured horticulture therapy programme led by a trained professional designed for people with high levels of anxiety or participating in a forest therapy programme led by a psychologist and designed for people suffering from prolonged grief.
Nature-based health promotion (NBP)	**Nature-based health promotion** uses organised activities to support people to engage with nature, leading to improvements in health and well-being. These initiatives offer nature-based activities within an organised structure without specific therapeutic aims. Examples of NBP activities: walking in nature as part of walking groups promoted by the local health department or participating in an organised community gardening initiative.
Nature-in-everyday life (NEL)	**Nature-in-everyday life** provides opportunities for engagement with nature as part of people’s everyday lives, leading to improvements in health and well-being. Examples of NEL: spending time in a park near your home or growing vegetables and flowers in your home garden is passive engagement with nature.
Marginalised groups	Population groups that have fewer opportunities than other groups in society and may experience a higher risk of poverty, social exclusion, discrimination and/or violence than the general population due to social, cultural, economic and political conditions or a combination of these conditions. Some examples include, but are not limited to, racial or ethnic minorities, migrants, people living with disabilities, older people experiencing isolation, people experiencing unemployment and people belonging to the LGBTIQ+ (Lesbian, Gay, Bisexual, Trans, Intersex, and Queer and others) community.
Environmental justice	GreenME views **environmental justice** as fair and equal access to and benefit from environmental resources such as green care, regardless of one’s personal characteristics.

NBT, nature-based therapy.

It is well established that exposure to green, such as parks or gardens, or blue spaces, such as waterfronts or natural areas with prominent water features, is linked to better mental health, including lower levels of stress, depression and anxiety.^11^ For instance, one recent study indicates that transforming a third of the Barcelona city streets into green corridors could prevent between 8 and 14% of cases of various mental health problems, including more than 30 000 cases of self-perceived poor mental health yearly.^12^ Beyond everyday exposure to nature, growing evidence also supports the effectiveness of more targeted and tailored nature-based interventions for improving mental health. For example, in a study with 36 middle-aged women in South Korea, it was found that 12 sessions of horticulture therapy significantly improved depressive, cognitive and anxiety outcomes compared with controls.^13^ Similarly, a systematic review of nature-based health promotion (NBP) programmes (ie, green exercise and spending time ‘savouring’ nature) for workers reported significant positive effects on mental health and well-being in most studies.^14^

Increasingly, inequities in the nature-health relationship have been acknowledged. Environmental psychology and epidemiology studies suggest that marginalised individuals may experience relatively greater benefits from everyday exposure to nature, perhaps due to the comparative lack of access to other healthful resources or having worse initial health outcomes and thus greater potential for improved outcomes.^15–17^ Conversely, social science research highlights that green and blue spaces closer to where marginalised individuals live are often of lower quality,^18^ and that these environments can be perceived sometimes as unsafe due to personal or community-linked histories of hostility or violence in these spaces.^19–21^ Moreover, recent studies have linked the improvement of green and blue spaces with sustainability gentrification processes, which may further exclude marginalised groups from benefiting.^22–24^ NBP and nature-based therapy (NBT) activities may also be less accessible to these groups due to time, cost or caregiving constraints. Finally, the limited integration of nature-based approaches into healthcare systems means that those who might benefit most often have the least access.

Our project, Advancing Greencare in Europe, an integrated multi-scalar approach for the expansion of nature-based therapies to improve mental health equity (GreenME) is grounded in the assumption that the role of green and blue spaces in improving mental health equity can be better approached through a green care framework that highlights the interconnectedness of three levels: nature-in-everyday life (NEL), NBP and NBT. Our understanding of green care purposefully diverges from published definitions, which often restrict it to individualised, facilitated interventions^25
26^ or overlook the role that everyday contact with nature plays in supporting mental health and wellbeing.^27–29^ The aim of GreenME is to conceptualise all three levels of green care as components of essential health infrastructure, identifying context-specific challenges and opportunities and providing robust evidence to support political and financial investment in effective and equitable nature-based care, with additional social and ecological co-benefits.^30^

## Methods

Over a period of 4 years (Sept 2023—August 2027), GreenME employs a three-phase process ((i) diagnosis, (ii) increasing the scientific evidence and (iii) empowering green care actors) to better understand the ways in which effective green care strategies might be scaled up to improve adult mental health and well-being equity across Europe and beyond. Throughout, GreenME prioritises learning from existing green care interventions. It uses a transdisciplinary approach—consisting of co-creation methodologies and the incorporation of both academic and non-academic stakeholders in the design of research protocols—and is informed by a health equity and environmental justice framework. Half of the consortium partners are non-academic entities, including NBT providers, green care associations or local governments. The project also benefits from a multi-disciplinary advisory board which includes researchers, practitioners and policy-makers.

### Geographic scope

GreenME is being carried out in seven countries (Germany, Italy, Poland, Spain, Sweden, the UK and the US) with a variety of green care delivery partners and with healthcare structures. In each country, specific study areas represent regions with (i) diverse natural characteristics and levels of urbanicity and (ii) large populations of marginalised groups (as defined above). The specific study areas were used for the diagnosis phase of the project. In each of the specific study areas (see figure 1), sub-areas were selected for evaluating the role of NEL, NBP and NBT. In each sub-area, more than 50% of the population is socioeconomically deprived (ie, within the fourth and fifth quintiles of material and socioeconomic deprivation indexes available in each study area). In four of the seven countries where NBTs have a greater presence, we also evaluate existing NBTs. The evaluated NBTs (see table 2) are in the sub-areas.

**Table 2 T2:** NBT cases in those countries where trials are being conducted

Name	Target population	Type of therapy
Italy		
SalusSpace	Adults living or working in Bologna city	Horticultural
BattimareSpace	Adults living or working in Bologna city	Horticultural
Spain		
CSMaresme	Adults that attend a mental health centre that is part of a day hospital	Horticultural
PSStJoanDéu	Adults who are grieving a loss and are participating in a grief support group in an institution that is part of the healthcare system	Forest bathing
Sweden		
Shrinyin-yoku	Adults who attend mental health centres in the Stockholm area	Forest bathing
United Kingdom		
Tonic	Adults with mental health problems referred to the programme by doctors, community mental health teams other charities or self-referred	Surf
Northern Roots	Adults with mental health problems referred to the programme by doctors, community mental health teams, other charities or themselves	Horticultural

**Figure 1 F1:**
[figure not shown]
GreenME study areas analysed in Phase 1 (in italics) and sub-areas analysed in Phase 2 (in bold).

### Phase 1: diagnosis of green care status

Phase 1 (data collection completed in August 2024) aimed to diagnose the green care status in each of the study areas. Using a holistic approach with an environmental justice lens, informed by frameworks such as ‘health in all policies’,^31^ we first characterised a range of relevant actors and mapped key stakeholders at different scales of green care according to extent of influence and level of expertise. We then (1) conducted semi-structured interviews with key actors in each study area (see online supplemental annex 1 for the interview guide employed, which was also translated into the appropriate local language) and (2) conducted an analysis of grey literature. The grey literature items were sought by study teams in each country by searching the official websites of the stakeholders identified during the first phase (key actor mapping) of the research. The search covered documents, databases, information channels, guidelines or other resources that have been developed at the national, regional or local level and have been (1) prepared by or commissioned by public authorities/institutions or (2) recommended by public authorities/institutions. In the absence of such documents, grey literature items prepared by professional and scientific associations and non-governmental organisations of major importance dealing with (1) health and well-being or (2) green-blue spaces were taken into consideration. The aim was to examine a broad range of laws, planning and programming documents, guidelines and schemes that impact the existence of green and blue spaces and promote one or more of the three levels of green care. The grey literature items analysed related to specific fields which are relevant to green care, such as land-use planning, nature conservation, environmental protection, forestry, agriculture, land management, climate change, healthcare, social welfare, education, public statistics and public finances. The READ approach^32^ was used to analyse the grey literature documents to assess the complementarity of health and green and blue space policies, as well as other policies relevant to green care development.

Together, the interviews and grey literature analysis examined the state of implementation of the three levels of green care in each partner country and the challenges of scaling up existing successful initiatives in different health systems, geographical areas and management regimes, considering the barriers and challenges faced in each. In addition, using these two data sources, we explored the level of integration between different policies in terms of health, green and blue infrastructure, social equity and environmental justice from the perspective of local and regional governance. Results of Phase 1 will further inform Phase 2 and 3 analyses.

### Phase 2: increase scientific evidence for green care

Phase 2 consists of two sub-studies focused on (1) NBTs targeted for specific populations and (2) those aspects of green care (NBP and NEL) which have implications for the mental health (equity) of the general population.

#### Effectiveness, causal pathways and cost-effectiveness of NBT programmes

We first developed a theory of change to clarify how and through which causal pathways nature-based therapies are understood to improve adult mental health and well-being (equity), informed by the published literature and by an eDelphi consensus-making process to capture the diverse expertise of the consortium and sister project members. This process consisted of two iterative surveys—the first asking open-ended questions to respondents relating to the constructs commonly included in a theory of change (ie, inputs—resources to implement the programme or project, activities—actions taken using the inputs, outputs—immediate, tangible service or products delivered by the programme or project, outcomes—measurable short- to medium-term effects that occur due to the outputs and expected impact—long-term change that the programme or project aims to achieve).^33^ In the second survey, the responses to the first survey were processed into a series of unique statements. Respondents were then asked to rank each statement in terms of relevance and importance, and those statements which were agreed on as both important and relevant were then included in a final theory of change by members of the research team.

Consortium members, including NBT practitioners and academic researchers, then iteratively co-created a common general protocol to evaluate seven existing NBTs (see table 2 above). We started with a study design as close as possible to the ‘gold standard’ randomised-controlled trial, establishing standardised practices and procedures for data collection, processing and analysis; randomisation of participants and measurement tools which will be used across all cases. All seven trials will record: (i) characteristics of each NBT case, (ii) pre- and post-study contact with NEL and NBP, (iii) mental health and well-being, (iv) information on direct (ie, medical visits, inpatient stays, lab tests, drug consumption) and indirect medical costs (days on sick leave, reduced productivity) and (v) participant demographics; and qualitative data which will inform our understanding of (i) the mechanisms linking NBT to mental health outcomes and (ii) the differential mental health benefits linked to intersectional axes of power and privilege. The general protocol was then tailored for each specific NBT case, adapting those elements necessary to consider their unique possibilities, characteristics and challenges.

Finally, the adapted, tailored protocol is being implemented to evaluate each case. This sub-study is designed to achieve sufficient statistical power to explore the relationships between exposure to NBT and mental health outcomes and cost-effectiveness for each intervention. Additionally, a meta-analysis of data from all sites will be conducted. Findings will be instrumental in enabling the mainstreaming of NBT on a wider scale and provide crucial data on interventions and their effects.

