Our approach requires expertise from many sectors and disciplines, together forming a large, multi-cultural and transdisciplinary consortium to successfully employ the methods we propose here. Participants include academic researchers, local government administration representatives, providers of green care interventions and communication experts. In particular, the co-creation process requires extra efforts in mediating diverse goals and priorities expressed by green care implementers, decision-makers and academics. We have several administrative processes in place to bolster our ability to maintain contact and communications and ensure all consortium members reflect on their privileges (ie, holding regular check-ins with consortium partners, creating an agreed-upon list of common terms, opening participation in working groups to address more specific issues within the consortium to those who are interested and power and privilege reflective activities in each general assembly meeting).

However, GreenME’s approach has its challenges. Learning from existing interventions requires thoughtful consideration of the trade-offs between study design and practical feasibility. In evaluating existing NBTs, applying key features of randomised-control trials is often difficult and, in some cases, not possible (such as blinded randomisation, achieving sufficiently large sample sizes for cost-effectiveness analyses, standardising intervention features and others) while still respecting the integrity of the individual interventions. Nevertheless, much can be gained from this approach, particularly in building the evidence base needed to scale-up the use of NBT in the future and to develop long-term funding and operational frameworks that would otherwise remain beyond the scope of this study.

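### The assurance of sufficient power for cost-effectiveness in each nature-based therapy trial conflicts with the article's own statement on attainable sample sizes

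*Protocol article*

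**What the plan says.** Under the Methods heading on effectiveness, causal pathways and cost-effectiveness of NBT programmes, the article describes the evaluation of seven existing therapies, listed in its Table 2. The same core data, including direct and indirect medical costs, are collected throughout ("All seven trials will record"). The sub-study is then said to be "designed to achieve sufficient statistical power to explore the relationships between exposure to NBT and mental health outcomes and cost-effectiveness for each intervention". The next sentence provides for pooling: "Additionally, a meta-analysis of data from all sites will be conducted".

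The Discussion returns to the evaluation of existing NBTs and says that "applying key features of randomised-control trials is often difficult and, in some cases, not possible". Its examples include "achieving sufficiently large sample sizes for cost-effectiveness analyses", alongside blinding and standardisation of the intervention.

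The strengths and limitations box makes a general point: "The trade-offs of evaluating existing interventions may reduce the robustness of the study design". It mentions neither power nor sample size.

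**The concern.** The Methods sentence presents adequate power as a property of the design. It covers two kinds of outcome, and it applies to each intervention separately. The Discussion says that, for these same interventions, the sample size needed for one of those two outcomes may be out of reach. Both statements concern the same quantity, the number of participants available for a cost-effectiveness analysis.

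Cost-effectiveness is not a side issue. It appears in the abstract's list of project outputs, in the strengths and limitations box and in the title of the sub-study. The Methods section expects the findings to support wider adoption of NBT, and under Phase 3 the Phase 2 evidence goes to the workshops that draft national schemes. A reader who relied on the Methods sentence alone would take each programme's cost-effectiveness result as coming from an adequately sized trial. An inconclusive result could then be misread as evidence that a programme is not cost-effective, and a chance favourable result could be given too much weight.

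**Working it through.** The article states no sample size, significance level, power percentage, effect size, standard deviation or willingness-to-pay threshold. There is no figure to reproduce, so the check is a comparison of the two statements.

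**1. Scope of the Methods statement.** It names mental health outcomes and cost-effectiveness together and applies to each intervention. The article counts seven trials. Nothing limits the statement to certain trials, to one outcome or to the pooled analysis.

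**2. Role of the meta-analysis.** It is introduced as an addition, so it supplements the per-intervention claim and does not replace it. The article also does not say that the meta-analysis covers costs.

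**3. Scope of the Discussion statement.** It concerns the existing NBTs, which are the programmes in these trials. It names sample size for cost-effectiveness as one of several features that are often difficult and sometimes impossible to apply. It does not say which feature fails in which trial.

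**4. Comparison.**

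| | Methods, Phase 2 | Discussion |
|---|---|---|
| Programmes | each of the seven NBTs | the existing NBTs being evaluated |
| Mental health power | sufficient by design | not addressed |
| Cost-effectiveness power | sufficient by design | adequate sample size often difficult, in some cases not possible |

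The second row holds no conflict. The third does: sufficient power in every trial requires an adequate sample in every trial, and the Discussion does not claim that this can be had.

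**5. Why a shortfall matters (illustration on assumed inputs).** Assume a two-sided 5% level and a trial that reaches a fraction f of its required size. By the normal approximation,

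power = Φ[(z₀.₉₇₅ + z_design) × √f − z₀.₉₇₅],

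with z₀.₉₇₅ = 1.960 and z_design = 0.842 (80% design power) or 1.282 (90%). For 80% design power and f = 0.6: 2.802 × 0.775 − 1.960 = 0.210, and Φ(0.210) = 0.58.

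| Fraction of required size reached | Designed for 80% | Designed for 90% |
|---|---|---|
| 0.8 | 71% | 83% |
| 0.6 | 58% | 71% |
| 0.5 | 51% | 63% |

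These figures show only how quickly adequate power is lost when the size is missed. They are not estimates for any of the seven trials, because the article gives no shortfall.

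**The case against.** The best defence is that the two statements are of different kinds. The Methods sentence expresses a design aim, in the soft language of exploring relationships. The Discussion gives an honest feasibility caveat, and aims and caveats can coexist. The caveat also covers a list of features, so it does not strictly say that the cost-effectiveness sample is the one that is impossible in some trials. The limitation is disclosed, the design is described only as being as near to a randomised trial as practice allows, and the trial-specific protocols, which are not shown, may contain proper calculations.

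Much of this stands. It rules out several stronger readings that a reader might infer:

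- **That the trials are underpowered for cost-effectiveness.** The article states no size or power, and its caveat does not identify the trials affected. Some or all of the seven may be adequately sized.
- **That power for mental health is also in doubt.** The Discussion names sample size only in connection with cost-effectiveness.
- **That the trials were sized on a mental health outcome, leaving cost-effectiveness short.** Nothing in the article gives the basis for sizing.
- **That a power figure for cost-effectiveness can be derived.** It would need an assumed threshold, cost difference and variances. The answer would follow from those choices, including whether NBT is taken to add or save cost.

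The defence does not remove the conflict. Even as an aim, sufficient power is a claim about sample size. The Methods sentence makes it for every intervention without qualification or reference to the caveat. Disclosure ten paragraphs later does not correct an unqualified sentence. The point does not rest on a missing calculation, so the unseen protocols do not answer it, although they are where the sponsor can settle it.

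**Conclusion.** The point holds as an internal contradiction about cost-effectiveness. The per-intervention assurance cannot stand for all seven trials as written, because the article itself doubts that the required samples can always be reached. Its size is qualitative: one of the two outcomes in the power statement is affected, in an unspecified number of the seven trials, by an unspecified amount. The conclusion rests on reading the Discussion's caveat as applying to the evaluated NBTs, which is what its wording says. It does not depend on the illustrative power figures. The consequence is for interpretation: where the size is not met, a single trial cannot support a firm conclusion on whether its programme is cost-effective.

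**What to change.** Reconcile the two sections.

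- **Power statement.** Limit the Methods sentence to the outcomes and trials that were actually sized for it. The sponsor should confirm these from the trial-specific protocols and name any trials sized for cost-effectiveness. The sizing basis should not be written in without that confirmation.
- **Trials not sized for cost-effectiveness.** State that the analysis is estimation: incremental net benefit, or differences in cost and effect, with intervals. Draw no conclusion for that programme as to whether it is cost-effective.
- **Pooled analysis.** If costs are included in the meta-analysis, say so and state the precision it can be expected to reach.

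The trials are already under way according to the project status section, so this should be settled before cost-effectiveness results are known. A later change in the standing of these analyses could look driven by the data. The cost is a less favourable claim and some rewording. No extra participants are needed.
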